### 17.4 Recording & Reporting Serious Adverse Events or Reactions:

All adverse events should be reported. Depending on the nature of the event, the reporting procedures below should be followed. Any questions concerning adverse event reporting should be directed to the Chief Investigator, Senior Trial Manager or Trial Manager in the first instance. A flowchart (figure 1) is given below to aid in the reporting procedures.

**Adverse Event (including Adverse Reaction):** All non-serious adverse events / reactions during drug treatment will be reported on the trial CRF. Severity of AEs will be graded on a three-point scale (mild, moderate, severe). Relation of the AE to the treatment should be assessed by the investigator at site. The Chief Investigator will be responsible for managing all adverse events/reactions.

**Serious Adverse Event / Reaction (SAE/SAR, including SUSARs):** All SAEs, SARs & SUSARs during drug treatment shall be reported to the Chief Investigator within 24 hours of the site learning of its occurrence. The initial report can be made by completing the serious adverse event CRF and faxing it via the SoHO66 fax to email system which will automatically send email notification to the Chief Investigator and to NCTU. In the case of incomplete information at the time of initial reporting, all appropriate information should be provided as follow-up as soon as this becomes available. Relationship of the SAE to the treatment should be assessed by the investigator at site, as should the expected or unexpected nature of any serious adverse reactions.

The MHRA and main REC will be notified by the Chief Investigator (on behalf of the Sponsor) of all SUSARs occurring during the trial according to the following timelines; fatal and life-threatening within 7 days of notification and non-life threatening within 15 days. SUSARs will be reported using a CIOMS 1 form, specifying the EudraCT number, CTA number, protocol number and trial name, and the data elements listed in Annex 3 of *Detailed guidance on the collection, verification and presentation of adverse reaction reports arising from clinical trials on medicinal products for human use – April 2006*.

All investigators will be informed of all SUSARs occurring throughout the trial on a case-by-case basis.

The Chief Investigator will ensure the Newcastle upon Tyne Hospitals NHS Foundation Trust as Sponsor is notified of any SUSARs in accordance with local trust policy.

Local investigators should report any SUSARs and / or SAEs as required by their local Research & Development Office.

## 17.5 Pregnancies

If a female participant does become pregnant while participating in the trial, trial drug will be discontinued immediately. Details of the pregnancy should be reported to NCTU within 24 hours of learning of its occurrence. The pregnancy must be followed up to determine outcome. Additional follow-up will no longer be required once the newborn is determined to be healthy.

## **18. Ethics & Regulatory Issues**

The conduct of this trial will be in accordance with the recommendations for physicians involved in research on human subjects adopted by the 18th World Medical Assembly, Helsinki 1964 and later revisions.

Favourable ethical opinion and Clinical Trial Authorisation from relevant Competent Authority (ies) will be sought prior to commencement of the trial. Local approvals will be sought before recruitment may commence at each site. Copies of these approvals will be kept in the Trial Master File at NCTU and in the Investigator Site File at local site.

Information sheets will be provided to all eligible subjects and written informed consent obtained prior to any trial procedures. For subjects who cannot consent for themselves, an appropriate independent witness will provide written consent.

## **19. Confidentiality**

Personal data will be regarded as strictly confidential. To preserve anonymity, any data leaving the site will identify participants by their initials, a unique trial identification code and date of birth. The trial will comply with the Data Protection Act, 1998. All trial records and Investigator Site Files will be kept at site in a locked filing cabinet with restricted access.

All laboratory samples will be labelled with a unique trial identification number and patient date of birth only (linked in anonymised form).

### **19.1 Safeguarding confidentiality**

Data collection and transfer in this trial will comply with NRES and Caldicott guidelines and the Data Protection Act (1998). All patients will be allocated a unique study identifier, which will be used on all eCRFs and paper questionnaires to preserve confidentiality; names or addresses will not appear on completed questionnaires or case report forms. Only a limited number of members of the research team will be able to link this identifier to patient-identifiable details (name & address) which will be held on a separate password protected database in NCTU.

All trial documentation will be held in secure NCTU offices, not open to the public and all members of the research team with access to identifiable or anonymised data will operate to a signed code of confidentiality. Transmission of hard-copy records (e.g. CRFs, questionnaires, SAE reports) between site and the NCTU will be by secure fax, post or hand delivery by the research nurses / trial manager.

Participants will be informed in the patient information sheet about the transfer of information to the NCTU and about levels of access to patient identifiable data, and will be asked to consent to this. Any data used in publications from this trial will be fully anonymised; it will not be possible to identify individual patients from such publications.

Trial data will be entered from source, into a FDA CFR 21part 11 compatible clinical data management software package (MACRO Database system) for processing and management, allowing a full audit trail of any alterations made to the data post entry.

All personal information obtained for the trial will be held securely at the trial site and will be treated as strictly confidential. Site number, screening and randomisation codes will permit the removal of much personal detail (e.g. name and address) prior to transfer of data to the trial office in NCTU.

### **19.2 Long term data storage**

At the end of the trial, original questionnaires, case report forms and consent forms will be securely archived for 15 years following publication of the last paper or report from the trial, in line with Sponsor policy and standard operating procedures. This will also allow any queries or concerns about the data, conduct or conclusions of the trial to be resolved.

## 20. Insurance and Finance

The Newcastle upon Tyne Hospitals NHS Foundation Trust has liability for clinical negligence that harms individuals toward whom they have a duty of care. NHS Indemnity covers NHS staff and medical academic staff with honorary contracts conducting the trial for potential liability in respect of negligent harm arising from the conduct of the trial. The Newcastle upon Tyne Hospitals NHS Foundation Trust is Sponsor and through the Sponsor, NGS indemnity is provided in respect of potential liability and negligent harm arising from trial management. Indemnity in respect of potential liability arising from negligent harm related to trial design is provided by NHS schemes for those protocol authors who have their substantive contracts of employment with the NHS and by Newcastle University Insurance schemes for those protocol authors who have their substantive contract of employment with the University. This is a non-commercial trial and there are no arrangements for non-negligent compensation.

- Wellcome Trust are funding the trial
- Creabilis are providing CT327 free of charge for the duration of the treatment phase of the trial.

## **21. Trial Report / Publications**

The data will be the property of the Chief Investigator and Co-Investigator(s). Publication will be the responsibility of the Chief Investigator.

It is planned to publish this trial in peer review articles and to present data at national and international meetings. Results of the trial will also be reported to the Sponsor and Funder, and will be available on their web site. All manuscripts, abstracts or other modes of presentation will be led by the TMG and circulated to the Trial Steering Committee and Funder prior to submission. Individuals will not be identified from any trial report.

Participants will be informed about their treatment and their contribution to the trial at the end of the trial, including a lay summary of the results.

## 23. Appendices

### 23.1 Appendix A

- **Modified Draize score test**

| Score | Grade                    | Definition                                                                            |
|-------|--------------------------|---------------------------------------------------------------------------------------|
| 0     | Clear                    | Normal skin surface                                                                   |
| 1     | Almost Clear             | Just perceptible erythema and just perceptible papulation/infiltration                |
| 2     | Mild inflammation        | Mild erythema and mild papulation/infiltration                                        |
| 3     | Moderate inflammation    | Moderate erythema and moderate papulation/infiltration                                |
| 4     | Severe inflammation      | Severe erythema and severe papulation/infiltration                                    |
| 5     | Very Severe inflammation | Severe erythema and severe papulation/infiltration with oozing/crusting or ulceration |

## 23.2 Appendix B

### Patient treatment questionnaire

(Please tick one box for each question)

#### 1. How did you find application of the ointment

- ☐ Easy
- ☐ Neither easy or difficult
- ☐ Difficult

#### 2. How long did it take to apply study treatment?

- ☐ Less than 1 minute
- ☐ More than 1 minute but less than 5 minutes
- ☐ More than 5 minutes but less than 10 minutes
- ☐ More than 10 minutes

#### 3. Overall, how satisfied were you with study medication?

- | Very satisfied           | Satisfied                | Neither
satisfied or
dissatisfied | Dissatisfied             | Very
dissatisfied     |
|--------------------------|--------------------------|-----------------------------------------|--------------------------|--------------------------|
|  |  |                 |  |  |

#### 4. If this ointment was available as a treatment would you use it?

- ☐ Yes
- ☐ No

#### 5. Cohort 2 participants only: Which side did you think was the active treatment side? (Please check with the research team if you are uncertain if this question applies to you.)

- ☐ My right
- ☐ My left
- ☐ I don't know

## 23.3 Appendix C

### PATIENT DIARY: Cohort 1

Study Number \_\_\_\_  
Patient Initials \_\_\_\_

| Day | Ointment Applied?
(please circle one) | Any issues or comments? |
|-----|------------------------------------------|-------------------------|
| 1   | Yes No                                   |                         |
| 2   | Yes No                                   |                         |
| 3   | Yes No                                   |                         |
| 4   | Yes No                                   |                         |
| 5   | Yes No                                   |                         |
| 6   | Yes No                                   |                         |
| 7   | Yes No                                   |                         |
| 8   | Yes No                                   |                         |
| 9   | Yes No                                   |                         |
| 10  | Yes No                                   |                         |
| 11  | Yes No                                   |                         |
| 12  | Yes No                                   |                         |
| 13  | Yes No                                   |                         |
| 14  | Yes No                                   |                         |
| 15  | Yes No                                   |                         |
| 16  | Yes No                                   |                         |
| 17  | Yes No                                   |                         |
| 18  | Yes No                                   |                         |
| 19  | Yes No                                   |                         |
| 20  | Yes No                                   |                         |
| 21  | Yes No                                   |                         |
| 22  | Yes No                                   |                         |
| 23  | Yes No                                   |                         |
| 24  | Yes No                                   |                         |
| 25  | Yes No                                   |                         |
| 26  | Yes No                                   |                         |
| 27  | Yes No                                   |                         |
| 28  | Yes No                                   |                         |

| Month              | Side  | DAY ( From ____ / ____ / ____ - To ____ / ____ / ____ ) |   |   |   |   |   |      |      |      |    |    |    |    |    |    |    |    |    |    |    |    |    |    |      |      |      |    |    |
|--------------------|-------|---------------------------------------------------------|---|---|---|---|---|------|------|------|----|----|----|----|----|----|----|----|----|----|----|----|----|----|------|------|------|----|----|
|                    |       | 1                                                       | 2 | 3 | 4 | 5 | 6 | 7    | 8    | 9    | 10 | 11 | 12 | 13 | 14 | 15 | 16 | 17 | 18 | 19 | 20 | 21 | 22 | 23 | 24   | 25   | 26   | 27 | 28 |
| For Example |       | ✓                                                       | ✓ | ✓ | ✓ | ✓ | ✓ | ✓ S1 | ✓ S1 | ✓ S1 | ✓  | ✓  | M  | ✓  | ✓  | ✓  | ✓  | ✓  | ✓  | W  | ✓  | ✓  | ✓  | ✓  | ✓ S2 | ✓ S2 | ✓ S2 | ✓  | ✓  |
| 1                  | Left  |                                                         |   |   |   |   |   |      |      |      |    |    |    |    |    |    |    |    |    |    |    |    |    |    |      |      |      |    |    |
|                    | Right |                                                         |   |   |   |   |   |      |      |      |    |    |    |    |    |    |    |    |    |    |    |    |    |    |      |      |      |    |    |
| 2                  | Left  |                                                         |   |   |   |   |   |      |      |      |    |    |    |    |    |    |    |    |    |    |    |    |    |    |      |      |      |    |    |
|                    | Right |                                                         |   |   |   |   |   |      |      |      |    |    |    |    |    |    |    |    |    |    |    |    |    |    |      |      |      |    |    |
| 3                  | Left  |                                                         |   |   |   |   |   |      |      |      |    |    |    |    |    |    |    |    |    |    |    |    |    |    |      |      |      |    |    |
|                    | Right |                                                         |   |   |   |   |   |      |      |      |    |    |    |    |    |    |    |    |    |    |    |    |    |    |      |      |      |    |    |

# 1. INTRODUCTION

This statistical analysis plan provides guidelines for the analysis and presentation for the analysis of Phase 1b (referred to as cohort 1 in the protocol) and Phase 2a (referred to as cohort 2 in the protocol) of the TRAC trial as per Protocol V2.1 26th August 2015. Unless otherwise stated, each section applies to both phases of the trial. This plan, along with other documents relating to the analysis of this trial, will be stored in the Statistical section of the Trial Master File.

## 1.1 Trial Summary

This is a non-commercial trial to determine the safety and preliminary efficacy of CT327 in patients with inherited CYLD defective skin tumours.

The trial is split into two phases namely a phase 1b which aims to determine the safety profile of CT327, and a phase 2a that will investigate if CYLD defective tumours respond to CT327.

Patients with germline mutations in a tumour suppressor gene called CYLD develop multiple, disfiguring hair follicle tumours on the head and neck. The prognosis is poor with up to 1 in 4 mutation carriers requiring complete surgical removal of the scalp. There are no effective medical alternatives to treat this condition.

This trial aims to repurpose a topical treatment with the potential to inhibit and possibly prevent tumour growth. Supported by a group of highly motivated patients, this work is driven by experimental data derived from rare, CYLD defective tumours. Whole genome molecular profiling experiments led to the discovery of an attractive molecular target in these skin tumour cells, named TRK.

Creabilis have recently developed an ointment (CT327) containing a TRK inhibitor (mini-pegylated – K252a). CT327 is an attractive, potentially novel agent for this condition as it is applied topically and already has safety data from human Phase 2b trials for the treatment of psoriasis and atopic dermatitis. This trial is designed to determine if the solution of delivering a small molecule to an inherited skin tumour model may represent a safe and feasible treatment for early tumours in these patients.

In Phase 1b the primary objective is to determine the safety of CT327 application in CYLD mutation carriers. The primary outcome will be the number of patients with severe treated skin site reactions as determined by Modified Draize score.

Secondary outcomes of Patient reported quality of life, acceptability of treatment and adverse events within the 4 week treatment period will also be reported.

Phase 2a is a randomised double blind single site trial where the primary objective is to establish if CYLD defective tumours respond to CT327. The primary outcome will be the proportion of tumours responding to treatment by 12 weeks in both actively treated lesions and placebo treated lesions.

Secondary outcome measures will be change in tumour volume, adverse events, compliance, confirmation of the definition of response, expression of targets of TRK signalling in tumour biopsies, patient reported quality of life according to EQ5D and DLQI, acceptability of treatment and a trial specific pain measure.

To achieve the 150 tumours required 15-20 patients will be recruited in Phase 2a.

More detailed information regarding the trial can be found in Protocol V2.1 26th August 2015.

## 2. TIMING AND REPORTING FINAL ANALYSES

Analysis of Phase 1b data planned at milestone 2 as documented in the trial master file.

Phase 1b: Data entry will be completed by 24/04/2015.

After completion of database reports and checks the data will be released to the trial statistician no later than 13/05/15.

Dummy tables will be populated by and the report circulated approximately a week in advance of the Data Monitoring Committee (DMC) meeting which will take place on 29/05/15.

Final analysis of Phase 2a data is planned with all recruited patients treated and followed for a minimum of 4 weeks at the end of milestone 3, which is 20 months from trial start date, anticipated November 2016, as documented in the trial master file.

Interim analyses will be presented to the Trial DMC planned at the end of phase 1b recruitment and mid-way through phase 2a recruitment, planned at milestone 2, 13 months from start date, anticipated January 2016. Snapshots for data cleaning purposes, without identification of treatment group, may be taken prior to snapshots of data used for reporting. Unless the DMC request increased frequency due to safety concerns. There are no statistical stopping criteria since the trial is not designed around hypothesis testing.

## 3. RECRUITMENT AND RANDOMISATION

### 3.1 Recruitment

The following will be reported on:

- Date of snapshot and data-lock (final analysis).
- Report dates when trial opened, last patient entered (interim) and closed to recruitment (final).
- Consort diagram (Appendix 1)
- Plot of recruitment over time.

### 3.2 Randomisation: Phase 2a only

Randomisation is at the per patient level randomising active and placebo treatments to left or right sided application. There are no stratification factors.

Four or five tumours matched for size will be selected on each side of the patient. Each tumour will be assigned a number to facilitate assessments and then each side of the patient will be allocated randomly to receive either active ointment or placebo ointment.

The number of tumours and unique number of patients recruited will be reported. The number of tumours in each of active and placebo group will be reported.

### 3.3 Ineligible Patients

Ineligible patients are classed as those patients who are found to subsequently not adhere to the eligibility criteria of the trial. The number of ineligible patients and reasons for ineligibility will be reported. Protocol violators will be reported as part of treatment compliance (section 5.2). Any patients found to be ineligible after entry to the trial will remain in the ITT analysis but may be excluded from the treatment set.

## **4. DATA QUALITY**

### **4.1 Forms Returned**

Data are collected using electronic case report forms (CRF) as detailed in the Data Management Plan (DMP). Completion rates for each CRF will be reported as specified in the DMP. A full listing of CRF's requested are specified in the DMP.

## **5. STUDY POPULATION**

### **5.1 Defining Populations for Analysis**

All patients recruited to Phase 1b will be known as the Phase 1b trial set and to 2a the Phase 2a trial set, as intention to treat sets.

All eligible patients/tumours who start treatment in phase 1b will be known as the Phase 1b treatment set and in Phase 2a the Phase 2a treatment set.

All eligible patients/ tumours who start and complete 12-weeks of treatment in phase 2a will be known as the Phase2a protocol set. If further subsets emerge they will be named appropriately.

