## **7. SAFETY ANALYSIS**

Most adverse events (AE) and adverse drug reactions that occur in this trial, whether they are serious or not, will be expected treatment-related toxicities due to the drugs used in this trial. For a full list of expected undesirable effects of CT327, please refer to the Investigator Brochure.

AE's are recorded by the clinical staff directly to the database on a three-point scale of severity (mild, moderate or severe) and also by causality (relationship to treatment categorised on a six point scale), as described in the protocol.

The analysis sets are the Phase 1b treatment set and the Phase 2a treatment set.

Any adverse events/reactions from start of treatment and up to the time of tumour excision (Phase 1b) or 4 weeks after end of treatment (Phase 2a), will be categorised according to severity and causality and recorded on the database.

The number of patients (Phase 1b) and tumours (Phase 2a) reporting any AE will be reported clarifying those deemed to be treatment related (Appendix 2).

In Phase 2a, the number of tumours with at least one AE will be reported as a proportion of the total number of tumours. The number of tumours with at least one treatment-related AE, that is those described as definitely, probably or possibly related, will be reported as a proportion of the total number of tumours. The number of tumours with at least one 'moderate' or 'severe' treatment-related AE will be reported as a proportion of the total number of tumours.

The unique number of patients experiencing at least one 'moderate' or 'severe' treatment-related AE will be reported as a proportion of the treatment set.

Proportions will be presented as % (95% CI).

Descriptions of the adverse events may require listing in the text.

No significance testing will be carried out.

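### The SAP tabulates adverse events on a treatment set limited to eligible patients, so events in exposed patients later found ineligible can drop out, and systemic events in Phase 2a have no proper table.

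*Combined protocol and SAP*

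**What the plan says.** **Who is in each set.** SAP 5.1 defines two sets that matter here. The trial set is everyone recruited: "All patients recruited to Phase 1b will be known as the Phase 1b trial set and to 2a the Phase 2a trial set". The treatment set is narrower: "All eligible patients/tumours who start treatment in phase 1b will be known as the Phase 1b treatment set", with a parallel definition for Phase 2a. No set is defined as all patients or tumours exposed to the ointment.

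**What happens to ineligible patients.** SAP 3.3 makes ineligibility something established after entry: "Ineligible patients are classed as those patients who are found to subsequently not adhere to the eligibility criteria of the trial". Such patients "will remain in the ITT analysis but may be excluded from the treatment set". Their number and the reasons are to be reported. Nothing is said about reporting their AEs.

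**Which set the AE analysis uses.** SAP 7: "The analysis sets are the Phase 1b treatment set and the Phase 2a treatment set". For Phase 2a, "the number of tumours with at least one AE will be reported as a proportion of the total number of tumours", and treatment-related events are counted per tumour in the same way. The table shell in SAP Appendix 2 has active and placebo columns. The one patient-level count that covers Phase 2a is restricted to moderate or severe related events: "treatment-related AE will be reported as a proportion of the treatment set".

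**What other sections say.** SAP 1.1 and the protocol summary (4.1, 4.2) list AEs as a secondary outcome in both cohorts. SAP 8.2.3 assigns secondary outcomes to the trial sets. Protocol 14.1 says all recruited patients contribute in cohort 1, and all randomised tumours in cohort 2.

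**The concern.** A safety summary should describe everyone who was exposed. Eligibility is a different question, and here it can be settled after exposure and after an event has been seen. SAP 5.1 reads as if ineligible patients are always outside the treatment set, while SAP 3.3 makes exclusion optional. Neither says who decides, by what criterion, or when relative to AE review or unblinding. In cohorts of 8 and of 15 to 20 patients, one such decision visibly changes the AE table.

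The second part concerns the Phase 2a layout. Each patient treats one side of the body with CT327 and the other with placebo. A local reaction belongs to a tumour and a side, but a headache or a bout of diarrhoea does not. The plan has no rule for placing such events in a tumour-by-arm table, and its only patient-level count omits mild events and those judged unrelated.

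At stake is the completeness of the reported AE profile in what protocol 10.1 describes as the first trial of CT327 in this population.

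**Working it through.** The plan states no figure on this point, so there is nothing to reproduce. The check is a trace of the definitions, then simple arithmetic for scale.

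**1. Trace of one patient.** Suppose a patient is recruited, applies the ointment, has a non-serious AE and is then found to have breached an entry criterion.

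| Place | Set used | Patient counted? |
|---|---|---|
| SAP 7, AE tables | Treatment set (SAP 5.1, 3.3) | Can be removed |
| SAP 8.2.3, secondary outcomes | Trial set | Yes |
| Protocol 14.1 | All recruited patients / all randomised tumours | Yes |
| SAP 8.2.1, Phase 1b Draize primary | Trial set | Yes |
| Protocol 17.4, SAE and SUSAR reporting | No analysis set involved | Would be reported if serious |

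Two analysts following different sections could produce different AE tables from the same data.

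**2. Scale, cohort 1.** Input: 8 patients (protocol 14.2). Assumption: one exposed patient is excluded.

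- Share of exposed patients lost: 1/8 = 12.5%.
- If that patient had the only event, the rate goes from x/n to (x − 1)/(n − 1): 1/8 = 12.5% (exact 95% CI 0.3% to 52.7%) becomes 0/7 = 0% (0% to 41.0%).
- If the one event was in another patient, the rate goes from x/n to x/(n − 1): 1/8 = 12.5% becomes 1/7 = 14.3% (0.4% to 57.9%).

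The direction of the distortion therefore depends on who is excluded.

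**3. Scale, cohort 2.** Inputs: 15 to 20 patients, 8 to 10 tumours each, 150 tumours in all (protocol 4.2, 7.2). Assumption: one patient is excluded.

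- Patients: 1/20 = 5.0% to 1/15 = 6.7%.
- Tumours: 8/150 = 5.3% to 10/150 = 6.7%.
- If that patient had the only event, 1/15 = 6.7% (0.2% to 31.9%) becomes 0/14 (0% to 23.2%), or 1/20 = 5.0% (0.1% to 24.9%) becomes 0/19 (0% to 17.6%).

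**4. Events that fit no arm.** Protocol 17.2 lists 17 event terms from previous studies. Nine are plainly systemic: headache, nasopharyngitis, diarrhoea, rhinitis, upper respiratory tract infection, cough, back pain, fatigue and vomiting. So 9 of the 17 terms cannot be assigned to a tumour or to active versus placebo. Under SAP 7, such an event reaches a defined patient-level count only if it is both moderate or severe and treatment-related. A mild headache, or a moderate one judged unrelated, has no defined cell.

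**The case against.** The strongest reply is that the exposure to error is narrow, and much of it stands.

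- **The primary safety outcome is outside the problem.** A reader might infer that all safety results in cohort 1 are at risk, since safety is its primary objective. They are not. SAP 8.2.1 reports severe reactions (Modified Draize 4 or 5) on the trial set, so an ineligible patient with a score still counts.
- **The progression decision is not shown to be affected.** A reader might take 4 of 8 patients with unexpected related events, remove one, and conclude that 3 of 7 would pass the limit of 3 patients in protocol 14.2 and 14.3. Those sections name no analysis set. Protocol 7.1 and SAP 8.4 base progression on severe skin reactions and the DMC's recommendations. SAP 2 also plans the Phase 1b DMC meeting for 29/05/15, whereas this SAP cites a protocol dated 26 August 2015.
- **Exclusion need not favour the drug.** A reader might infer that those removed would be the patients most likely to react. The documents do not support this. Recently changed tumours and concurrent illness are exclusions in cohort 2 only, and criteria such as surgery timing or contraception have no evident link to reactions.
- **Late ineligibility may be rare.** Eligibility is confirmed before enrolment or randomisation (protocol 9.3). Eligibility data are source-verified for all cohort 1 participants and half of cohort 2 (protocol 16.1).
- **Tumour-level counting suits a split-body trial.** Protocol 14.1 plans it, all AEs are recorded with severity and causality, and SAP 7 allows descriptions in the text. It would be too strong to say that systemic events must be lost or counted on every tumour.
- **The analysis is descriptive.** No test or design figure changes.

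It can also be argued that SAP 8.2.3 was not written with AEs in mind, since its subsections do not cover them. That removes part of the conflict, but it leaves SAP 7 governing and so makes the restricted set more likely to be used. None of these replies supplies an all-exposed set or a defined place for systemic events.

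**Conclusion.** The point holds for the AE tables in SAP 7. As written, AEs in exposed patients can leave both numerator and denominator on an eligibility finding made after exposure, under a rule with no criterion, and other sections of the plan point to a different population. It is a possibility, not a certainty: SAP 3.3 is permissive, and the documents give no expected number of ineligible patients. On the assumption of one, 12.5% of exposed patients are lost in cohort 1 and 5.0% to 6.7% in cohort 2.

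The layout point holds in a limited form. Systemic events, 9 of the 17 listed terms, cannot be placed by arm, and the patient-level count does not cover all of them. This is a gap in tabulation; the events are still recorded.

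The documents do not support extending either point to the Draize primary outcome, to SAE or SUSAR reporting, or to the decision to open cohort 2.

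**What to change.** 1. In SAP 5.1, add a safety set for each phase: every patient and tumour with at least one application, regardless of eligibility.
2. In SAP 7, use the safety set throughout, including for the patient-level proportion. Keep the eligible subset only as a sensitivity set.
3. In SAP 8.2.3, state that AEs are analysed on the safety set under SAP 7, and note how this relates to the populations in protocol 14.1. In SAP 3.3, state that ineligibility does not remove a patient from the safety set.
4. For Phase 2a, limit the tumour-by-arm table to application-site events. Tabulate all other AEs, of any severity and any causality, once per patient and without attribution to an arm.

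The cost is SAP wording and one extra table shell. The data are already collected, and no design figure changes.
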